## 2. Materials and Methods

### 2.1. Study Design

This is a protocol for a controlled single blinded clinical trial [20].

The project was approved by the Ethics Committee of the Federal University of Paraná under number 39816320.1.0000.0102. The WPEP study protocol was developed based on the recommendations for clinical trial protocols of the Standard Protocol Items: Recommendations for Interventional Trials (SPIRIT) [21]. This is a high-intensity aquatic physical exercise program to be conducted with individuals with a clinical diagnosis of PD, which will be assessed in two phases, prior to the start of the program and after its completion.

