### 2.4. Assessments

All assessments will be performed at the “on” stage of dopaminergic medication, approximately 1 h after intake. The assessment instruments will take place in three stages: Assessment 1 (initial), followed by 12 weeks of intervention or control period; Assessment 2, after the intervention period or control of the study; Assessment 3, after a 4-week follow-up (no intervention).  Figure 1 shows the sequence of evaluations and interventions.

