### 2.10. Statistical Analysis

The data will be analyzed for sphericity and homogeneity with Shapiro–Wilk test. The ANOVA mixed model will be used to compare pre- and postintervention and intergroup comparisons. Afterward, a Bonferroni post hoc analysis will be performed on variables with statistically significant differences to identify which assessments differ from each other. The statistical power will be *p* > 0.05, and the effect size will also be shown. SPSS 20.0 statistical software will be used in all the analyses.

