Studies that used the interval training methodology in individuals with PD performed on the ground employed activities that used treadmill and cycle ergometer [7, 11, 12, 15] with diversified parameterization. Malczynska-Sims et al. [15] performed 10 stages of 4 min, with 2 min for cycling in the fast stage and 2 min for the slow stage, and the training range was individualized and progressive according to the weeks and the maximum heart rate (60%–80%). Fernandes et al. [7] employed walking/jogging for 25 min with 1 min in the subjective perception of exertion 15–17 and 2 min between 11 and 13. Harvey et al. [11] conducted a feasibility study for HIIT using circuit dynamics and functional exercises, with four exercises performed at 85% of the maximal heart rate for 45 and 15 s of interval/rest without severe adverse effects. All these previous studies showed that HIIT on the ground is a safe modality for individuals with PD, in terms of adherence, participation, and increase in the physical and functional capacity. These findings may be used as a basis for interval training in an aquatic environment, since the literature on this subject is limited.

Finally, this WPEP was developed to assess this type of clinical intervention in PD population in an aquatic setting. The present clinical trial may have the following limitations: (1) the difficulty in recruiting and adhering to the study for 12 weeks plus the pre- and postintervention evaluation period; (2) the inability of participants to travel to the center where the study will be conducted, particularly Stage 4 participants; (3) difficulty in reaching target intensity due to changes in the autonomic nervous system and heterogeneity of the PD population. Furthermore, the WPEP does not include the use of an individual aquatic heart rate monitor (e.g., an aquatic heart rate monitor) during the intervention period to detect changes in the heart rate during immersion. All these limitations must be considered in future research.

However, details in the description of training and its prescription based on individuality and periodic progression, as well as easiness to apply and cost-effective assessments, may facilitate the WPEP clinical reproducibility.

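### The mixed ANOVA named in section 2.10 most naturally means a complete-case analysis, which would discard week-12 results for anyone who misses week 16; a likelihood mixed model would keep them

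*Protocol article*

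**What the plan says.** The analysis is set out in section 2.10 of the protocol article: "The ANOVA mixed model will be used to compare pre- and postintervention and intergroup comparisons". Three further statements there bear on what procedure is meant:

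- "The data will be analyzed for sphericity and homogeneity with Shapiro–Wilk test"
- "Bonferroni post hoc analysis will be performed on variables with statistically significant differences to identify which assessments differ from each other"
- "SPSS 20.0 statistical software will be used in all the analyses"

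No SPSS procedure is named.

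The schedule is described in two ways. Section 2.4 has three assessments: baseline, after the 12-week period, and "Assessment 3, after a 4-week follow-up (no intervention", which places the last at week 16. Section 2.1 instead describes a programme "which will be assessed in two phases, prior to the start of the program and after its completion".

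The Discussion lists as limitations "the difficulty in recruiting and adhering to the study for 12 weeks" (it adds the evaluation period) and "the inability of participants to travel to the center where the study will be conducted, particularly Stage 4 participants". Neither is tied to an arm. Section 2.9.6 gives 15 participants per arm.

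**The concern.** Sphericity is an assumption of the classical mixed-design (split-plot) ANOVA. A likelihood mixed model specifies the covariance instead. In SPSS the classical analysis is run with the repeated-measures GLM, which works on complete cases: one missing assessment removes the participant from every comparison.

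With three assessments in one model, a missed week-16 visit therefore erases a week-12 result that has already been collected. Week 12 is the end of the intervention period, where the comparison of the arms matters most. With 15 per arm each lost participant is costly, and the document expects some loss. If those lost differ between the arms in number and in how well they did, the remaining groups are no longer the randomised ones.

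**Working it through.** **Which procedure is meant.** With only two time points sphericity holds trivially, and there is only one pair of assessments to compare. The sphericity check and the Bonferroni step on which assessments differ therefore both fit a three-assessment split-plot ANOVA. That is the likeliest reading, but it remains an inference.

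**Figures in the plan.** The article gives no drop-out rate, SD or within-person correlation, so it has no figure of its own to reproduce here. All loss rates below are assumptions. The only input taken from the document is 15 per arm.

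**Precision.** For a difference of two means with equal SD, the standard error relative to full data is √[(1/n₁ + 1/n₂) / (1/15 + 1/15)].

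- 3 of 15 lost in one arm (12 and 15): √[(0.0833 + 0.0667)/0.1333] = √1.125 = 1.06, about 6% wider.
- 10 and 13 completers: √[(0.1000 + 0.0769)/0.1333] = √1.327 = 1.15, about 15% wider.

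**Bias, 15 per arm, simulated.** The change to week 12 is standard normal in both arms, with no true effect and a two-sided t-test at 5%. Three of 15 in one arm miss week 16 and are deleted; the other arm is complete.

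| Relation of loss to week-12 change | Shift in arm difference | False-positive rate |
|---|---|---|
| The 3 poorest are lost (correlation 1) | 0.33 SD | about 16% |
| Correlation 0.5 | about 0.16 SD | about 7% |
| None (random loss) | about 0 | about 5% |
| Nobody deleted (week-12 data kept) | 0 | about 5% |

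The shift favours whichever arm loses its poor responders.

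**Bias, drop-out rates in both arms.** Here there are three visits, SD 1 and correlation 0.5 between visits, so the SD of change is √[2(1 − 0.5)] = 1. Week-16 absence depends on the week-12 value or on the change to week 12. Positive values favour WPEP.

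| Assumed loss, WPEP/control | Complete cases | All available week-12 data |
|---|---|---|
| 20%/20% | about 0 | about 0 |
| 20%/10% | +0.06 to +0.11 SD | about 0 |
| 30%/10% | +0.11 to +0.22 SD | about 0 |
| 40%/10% | +0.16 to +0.32 SD | about 0 |
| 10%/30% | −0.11 to −0.21 SD | about 0 |

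**Limit of the remedy.** If participants leave before week 12 for reasons tied to the unseen week-12 value, the bias at 20%/10% to 40%/10% is +0.06 to +0.16 SD whether or not the available data are used.

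**The case against.** - **Listwise deletion is inferred.** The wording is also compatible with a likelihood mixed model in SPSS. The sphericity clue is weakened because the sentence attaches it to Shapiro–Wilk, which tests normality. This stands as a reason to call the text ambiguous. It does not make the complete-case reading unlikely.
- **The week-16 mechanism needs three assessments in one model.** Section 2.1 has two, and section 2.10 speaks of pre and post. Under a pre/post model a missed week-16 visit costs nothing at week 12. This stands, and is why the schedule must be reconciled.
- **A reader might infer that loss falls mostly on the WPEP arm and favours WPEP.** Twenty-four hospital sessions make greater WPEP loss plausible, but the documents do not support the claim. The stated limitations are not arm-specific. Exclusion after a medication change (section 2.9.1) applies to both arms. Controls may take up WPEP after week 12 (section 2.9.2), so their week-16 value is at risk too.
- **A reader might infer that those who stop training are not assessed.** The article says neither that they are nor that they are not. A condensed article may leave this to the full protocol, so its silence is no defect.
- **The 0.33 SD case is extreme.** It needs exactly the three poorest responders to go from one arm and nobody from the other. This stands; it is the upper end for a loss of three in one arm.

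**Conclusion.** The point holds in a limited form. Read most naturally, section 2.10 prescribes a complete-case analysis that would throw away collected week-12 results, in a trial of 30 that itself anticipates adherence and travel problems.

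The certain cost, once anyone is deleted, is precision: about 6% on the standard error for 3 lost from one arm, and about 15% with 10 and 13 completers.

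Bias is possible but conditional. It needs loss that is both unequal between the arms and related to outcome. For 3 of 15 lost in one arm the shift runs from about 0 (random loss) through about 0.16 SD to at most 0.33 SD, with false-positive rates of about 5%, 7% and 16%. Its direction cannot be known from the documents. The conclusion assumes the repeated-measures GLM and all three assessments in one model; if either fails, the week-16 mechanism disappears.

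**What to change.** 1. In section 2.10, replace the mixed ANOVA by a likelihood-based linear mixed model for repeated measures (SPSS MIXED), using every available assessment of all randomised participants in their allocated arm.
2. Reconcile sections 2.1 and 2.4 on the number of assessments, and say in section 2.10 which of them enter the model.
3. In section 2.4, state that participants who stop training are still invited to the assessments already scheduled. The model cannot remove bias from those who leave before week 12 for unobserved reasons, so obtaining their results is the only direct protection.

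The cost is wording in three sections, with the same software and no new visits in the schedule, though some people who have stopped training would be asked to attend. The statistical price is small: the model relies on a missing-at-random assumption and on a chosen covariance structure, which should be named in advance given 15 per arm.

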#### 2.9.2. Allocation

The allocation will be carried out randomly with support from the Sealed Envelope website (https://www.sealedenvelope.com/simple-randomiser/v1/lists). The subjects will be divided into an intervention group and a control group for a 12-week period. Following this period, participants in the control group will have the opportunity to participate in the WPEP.

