#### 2.9.4. Control Group

Individuals in the control group will be advised to maintain their usual physical activities for 12 weeks while avoiding high-intensity activities and/or swimming in a heated pool during the study period.

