#### 2.9.6. Sample Size

Based on the prevalence of individuals with PD in Curitiba, a sample calculation was performed using GPower 3.1. As a result, a sample of 30 individuals will be required, with 15 assigned to the intervention group and 15 assigned to the control group.

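### Section 2.10 names no between-group contrast as the efficacy test and does not adjust for baseline; a baseline-adjusted difference at Assessment 2 would be more precise and would remove the ambiguity

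*Protocol article*

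**What the plan says.** Section 2.10 fixes the model: "The ANOVA mixed model will be used to compare pre- and postintervention and intergroup comparisons". It then fixes a follow-up rule: "Afterward, a Bonferroni post hoc analysis will be performed on variables with statistically significant differences to identify which assessments differ from each other". It adds "and the effect size will also be shown". It names no baseline covariate, does not say which ANOVA term decides efficacy, and does not say which term must be significant before the post hoc step begins.

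The surrounding design is as follows:
- Allocation is random (section 2.9.2): "The subjects will be divided into an intervention group and a control group for a 12-week period".
- The comparator is usual activity (section 2.9.4): "Individuals in the control group will be advised to maintain their usual physical activities for 12 weeks".
- The size is given in section 2.9.6: "a sample of 30 individuals will be required, with 15 assigned to the intervention group and 15 assigned to the control group".
- Section 2.4 defines Assessment 1 (initial), Assessment 2 (after the 12 weeks) and Assessment 3 (after 4 further weeks). In section 2.10, assessments therefore most naturally means time points. Section 2.1 mentions only two phases, before and after the programme.

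**The concern.** Randomisation makes one question answerable without bias: did the intervention arm end up different from the control arm? A mixed ANOVA returns a time effect, a group effect and a group-by-time interaction, and these answer different questions. The time effect asks whether people changed, whichever arm they were in. The group effect averages in the pre-treatment value, which dilutes any treatment effect. Only the interaction carries the randomised comparison of change. Section 2.10 singles out none of them, and its one described follow-up is between time points.

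Two things are at stake. The first is clarity: several outcomes are effort-dependent tests done repeatedly (walking test, spirometry, respiratory pressures, sit-to-stand, TUG), so some improvement common to both arms is conceivable. The second is precision: with 30 people, the baseline value of every outcome is collected but is not used as a covariate.

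**Working it through.** **Inputs.** From the documents: 15 per arm (section 2.9.6), a mixed ANOVA without covariate (section 2.10), three assessments (section 2.4). Assumed: two-sided alpha 0.05, 80% power, equal SD at both assessments, and baseline-outcome correlation r between 0.3 and 0.9. Differences are in units of the between-person SD at one assessment.

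**The plan's own figure.** The total of 30 cannot be reproduced. Section 2.9.6 says only: "Based on the prevalence of individuals with PD in Curitiba, a sample calculation was performed using GPower 3.1". No effect size, SD, power or correlation is given. For reference, 15 per arm compared on the post value alone detects 1.06 SD with 80% power (t test, 28 df).

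**Precision.** With two time points, the group-by-time interaction is the t test on change scores.
- Variance per person of a change score: 2(1 − r).
- Variance per person of the outcome after adjusting for baseline: 1 − r².
- Ratio: (1 − r²) / [2(1 − r)] = (1 + r)/2.

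Detectable difference = k × √(2/15) × √(variance). By noncentral t, k = 2.902 for the change score (28 df) and 2.906 for ANCOVA (27 df, one spent on the covariate). So k√(2/15) is 1.060 and 1.061 respectively. Examples:
- r = 0.5: 1.060 × √1.00 = 1.06, against 1.061 × √0.75 = 0.92.
- r = 0.7: 1.060 × √0.60 = 0.82, against 1.061 × √0.51 = 0.76.

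| Assumed r | Variance ratio (1+r)/2 | Detectable, change score (SD) | Detectable, ANCOVA (SD) |
|---|---|---|---|
| 0.3 | 0.65 | 1.25 | 1.01 |
| 0.5 | 0.75 | 1.06 | 0.92 |
| 0.6 | 0.80 | 0.95 | 0.85 |
| 0.7 | 0.85 | 0.82 | 0.76 |
| 0.8 | 0.90 | 0.67 | 0.64 |
| 0.9 | 0.95 | 0.47 | 0.46 |

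Put as sample size, 30 people analysed by ANCOVA match about 30/0.75 = 40 analysed by change score at r = 0.5, and 30/0.85 = 35 at r = 0.7. For an assumed true difference of 0.8 SD, power by normal approximation is 59% against 72% at r = 0.5, and 81% against 87% at r = 0.7. The group main effect over two time points has only 20% to 27% power for that same difference, at r from 0.9 to 0.3.

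**Which term opens the post hoc step.** Suppose there is no treatment effect and both arms improve by 0.5 SD of the change score. This is an assumption; the documents give no expected change in controls. By simulation with 15 per arm:
- the time main effect is significant in about 75% of trials;
- the interaction is significant in 5%, its nominal level.

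If per-arm pre/post tests were then run at 0.05 (the text does not say that they would be per arm), significance in the intervention arm only would appear in about 23% of trials when a time or interaction term opens the step, but in about 2% when only the interaction does. The risk therefore depends almost entirely on a choice that section 2.10 leaves open.

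**The case against.** The strongest reply is that a between-group test is planned. Section 2.10 mentions intergroup comparisons, and the mixed ANOVA contains the interaction, which holds its 5% level. This stands: the plan does contain a valid test.

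A reader might infer more, namely that the plan counts within-group change as efficacy. The documents do not support this. No sentence says that a time effect or a change in one arm will be taken as benefit. The follow-up is conditional on a significant result, and the term that triggers it is simply not stated. The simulated percentages are conditional illustrations, not error rates of the plan.

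It can also be said that the change-score contrast is unbiased under randomisation, so the loss is one of efficiency. That is correct, and the loss is small at r of 0.8 or above. The equality with a change score also holds only for two time points; with all three assessments the interaction has 2 degrees of freedom.

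A further inference would be that anyone missing an assessment is dropped. That is true of a classical repeated-measures ANOVA, and the mention of sphericity leans that way, but the article does not say so and a likelihood-based model may be meant.

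Finally, such detail could be left to a fuller plan. That does not dispose of the point, because the article itself fixes a model and a follow-up rule.

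**Conclusion.** The point holds as a worthwhile improvement, not as an invalid analysis. Section 2.10 commits to a model without baseline adjustment, does not name the between-group contrast as the efficacy test, and describes only a comparison of time points as follow-up.

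For two time points, the ANCOVA variance is 65% to 95% of the change-score variance over r = 0.3 to 0.9. The detectable difference falls by 0.14 SD at r = 0.5 (1.06 to 0.92) and by 0.06 SD at r = 0.7 (0.82 to 0.76). These figures rest on an assumed r, equal SDs at the two assessments, alpha 0.05 and complete data on 15 per arm. The variance formula itself is certain; the size of the gain in this trial is not, because r is not stated. The possible misreading of a shared time effect as efficacy is allowed by the wording but not prescribed by it.

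**What to change.** Reword section 2.10 so that, for each primary outcome, efficacy is judged on the between-group difference at Assessment 2, adjusted for the baseline value of that outcome by ANCOVA and reported with a 95% CI. If Assessment 3 is brought into the same model, use a likelihood-based mixed model with baseline as covariate and group, visit and their interaction, and take the Assessment 2 contrast from it. Report within-group changes descriptively, without tests, and remove the Bonferroni comparison of assessments as a route to an efficacy claim.

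The precision argument supports the outcome's own baseline value as covariate; it does not require others, and section 2.9.2 names no stratification factor.

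The cost is one degree of freedom (28 to 27 with 30 people) and a wording change. No new data are needed, and the software already named can fit these models.

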Given the detailed description of this research protocol, if the WPEP provides positive results in terms of the evolution of PD symptoms through the assessed aspects, future studies using this methodology may be conducted to assist and guide the clinical practice of other health professionals who work with this population.

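### Comparisons between assessments are planned only for variables already found significant, so with 15 per arm a moderate true effect can get no group contrast at Assessment 2, and contrasts that pass tend to be too large

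*Protocol article*

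**What the plan says.** Section 2.10 of the protocol article sets out two steps. First, "The ANOVA mixed model will be used to compare pre- and postintervention and intergroup comparisons". Then, "a Bonferroni post hoc analysis will be performed on variables with statistically significant differences to identify which assessments differ from each other". The second step applies only to variables that passed the first. The section does not say whether the significant term must be time, group or their interaction.

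The same section adds "and the effect size will also be shown". No significance condition is attached to that promise, but no type, time point or interval is given either.

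Section 2.4 defines three assessments: baseline, the end of the 12-week period, and a third described as "Assessment 3, after a 4-week follow-up (no intervention)". Section 2.9.6 states that "a sample of 30 individuals will be required, with 15 assigned to the intervention group and 15 assigned to the control group". The Discussion says that, if results are positive, "future studies using this methodology may be conducted to assist and guide the clinical practice".

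**The concern.** The group comparison at the end of the 12 weeks is the natural measure of what the programme does. The article's only stated route to a comparison at a given assessment runs through a significance condition. That condition is not needed for error control among the contrasts of one variable, because Bonferroni protects that family without a preceding significant overall test.

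Two things follow in a small trial. A variable that misses the condition may be left with only a non-significant result, and the reader then cannot tell an inconclusive result with 15 per arm from evidence of little or no effect. A variable that meets it has been selected partly because its observed difference was large. Sections 2.5 and 2.6 list about 14 primary measures (the 6-minute walk, five heart rate variability indices, four spirometry measures, two respiratory pressures, two UPDRS sections), so the selection acts many times over. The results that come through are those on which the Discussion would base further work.

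**Working it through.** **What the article gives.** 15 per arm, two groups, three assessments. It gives no effect size, SD or correlation, and the sentence where a significance level is expected reads "The statistical power will be *p* > 0.05". The sample size is described only as "Based on the prevalence of individuals with PD in Curitiba, a sample calculation was performed using GPower 3.1", so 30 cannot be reproduced from stated inputs. Everything below therefore rests on assumptions: alpha 0.05 two-sided, SD 1, equal correlation r between assessments, no dropout.

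**How often the condition is met, if it is the group-by-time interaction.** Let the true group differences at the three assessments be (0, d2, d3) with mean m. The interaction test is F(2, 56), with critical value 3.16 and noncentrality

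λ = (n/2) × Σ(d − m)² / (1 − r), with n = 15.

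For (0, 0.5, 0.25): m = 0.25, Σ = 0.0625 + 0.0625 + 0 = 0.125, so λ = 7.5 × 0.125 / (1 − r) = 0.9375 / (1 − r). The last two columns come from 20,000 simulated trials per row and use the group difference in change from baseline at Assessment 2 (truth 0.50 SD).

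| r | λ | Met, exact | Met, simulated | Mean difference when met | Ratio to truth |
|---|---|---|---|---|---|
| 0.5 | 1.88 | 20% | 21% | 0.94 SD | 1.9 |
| 0.7 | 3.13 | 32% | 32% | 0.78 SD | 1.6 |
| 0.8 | 4.69 | 46% | 46% | 0.68 SD | 1.4 |

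So the contrast is not triggered in roughly 54% to 79% of such trials. Without the condition, the mean estimate is 0.50 SD. If the plain group difference at Assessment 2 is used instead of the difference in change, the ratio is lower: about 1.4 at r = 0.5 and 1.3 at r = 0.7.

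**How far this depends on the assumptions.**

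- Larger effect, high correlation: for (0, 0.8, 0.4) and r = 0.85, Σ = 0.32 and λ = 7.5 × 0.32 / 0.15 = 16. The condition is met in 95% of trials, with about 3% inflation.
- Smaller effect: with 0.3 SD at Assessment 2, r from 0.5 to 0.85 and all, half or none of the effect kept at Assessment 3, it is met in 10% to 32% of trials, with ratios of 1.6 to 2.6.
- Any significant term suffices, 0.5 SD, no common change over time, same ranges: met in 45% to 92%, ratios 1.03 to 1.28.
- Any significant term suffices, plus a change of 0.3 SD common to both groups, half the treatment effect kept, treatment effects of 0.3 to 0.8 SD: met in 69% to 100%, inflation at most about 7%.

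**The third assessment.** For a fully faded effect (0, 0.5, 0) and a fully retained one (0, 0.5, 0.5), Σ is 1/6 in both cases. At r = 0.7 both give λ = 7.5 × (1/6) / 0.3 = 4.17, and the condition is met in 41%. Half fading gives 32%.

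**A direct test without the condition.** The standard error of the difference in change is √(4(1 − r)/15). At r = 0.7 it is 0.283 SD, and with t(28) = 2.048 an estimate must be about 2.048 × 0.283 = 0.58 SD to be significant. With a true 0.5 SD this happens in 40% of trials, and the mean among significant results is about 0.76 SD, against 0.78 SD under the planned condition.

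**Width of the proposed intervals.** The 95% half-width, 2.048 × √(4(1 − r)/15), is about 0.75 SD at r = 0.5, 0.58 at 0.7 and 0.47 at 0.8.

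**The case against.** An ANOVA followed by Bonferroni comparisons is common practice and conservative. The sentence restricts tests; it does not say that group results at each assessment go unreported for other variables. The effect size is promised without a condition, and table content is often left to a fuller document. The size of the harm depends on a triggering term, an effect and a correlation that the article does not give. Most of this stands, and it limits the point in three ways.

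- A reader might infer that affected variables will certainly have no Assessment 2 estimate. The text does not support that. The promised effect size could turn out to be that estimate; its type and time point are simply not stated, so it is not guaranteed.
- A reader might infer that the overall test dilutes the effect by averaging in the no-training assessment. The interaction test does not work that way: it responds to the spread of the group differences, and full fading and full retention are equally detectable.
- A reader might infer that removing the condition cures exaggeration. It does not for results singled out by significance, which are about as inflated under a direct test. That inflation comes from 15 per arm.

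What does not stand is that the matter is mere omission. The condition is a rule the article fixes, and the only stated route to the comparison that matters most. The any-term reading offers limited comfort, since a significant time effect may be change common to both groups.

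**Conclusion.** The point holds as a risk created by a stated rule, not as a certain loss. Under a moderate true effect and a condition on the interaction, the Assessment 2 contrast would be triggered in about 21% to 46% of trials, and the reported difference would average 1.4 to 1.9 times the truth. These figures rest on an assumed 0.5 SD effect with half retained, correlations of 0.5 to 0.8 and alpha 0.05, none of which the article supplies. With large effects and high correlation the problem nearly vanishes; if any significant term suffices it is smaller, and slight when there is a common change over time. The gain from changing the rule is that every estimate becomes visible with its uncertainty, so that a non-significant outcome can be interpreted.

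**What to change.** In section 2.10, remove the significance condition for the between-group comparison. State that for every outcome, whatever the ANOVA result, the between-group difference in change from baseline at Assessment 2, and at Assessment 3, will be reported in the outcome's own units with a 95% confidence interval. Keep the Bonferroni adjustment for the tests across assessments, and name the ANOVA term that triggers any further post hoc tests. State that non-significant outcomes will be read from their intervals, and say what the promised effect size measures and at which assessment.

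This needs no additional participants or measurements. The cost is a change of wording and a fuller results table in which many intervals will be visibly wide.

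### The only inferential threshold in the article is labelled as power and written with the inequality reversed (Section 2.10)

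*Protocol article*

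**What the plan says.** Section 2.10 of the protocol article names the main analysis: "The ANOVA mixed model will be used to compare pre- and postintervention and intergroup comparisons". It then makes follow-up testing conditional on the result: "a Bonferroni post hoc analysis will be performed on variables with statistically significant differences". The criterion comes next: "The statistical power will be *p* > 0.05, and the effect size will also be shown". The section ends by naming the software.

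The other place where a significance level might appear is Section 2.9.6. It reads "Based on the prevalence of individuals with PD in Curitiba, a sample calculation was performed using GPower 3.1" and concludes that "a sample of 30 individuals will be required, with 15 assigned to the intervention group and 15 assigned to the control group". It does not state a significance level. Neither the Abstract nor the Discussion states one.

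**The concern.** The sentence contains two separate errors.

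- **The label.** Power is 1 − β, the probability of rejecting the null hypothesis when a specified effect is present. It is a property of the design and is not expressed as a bound on p.
- **The direction.** A significance rule declares a difference when p falls below alpha. The sentence has p above 0.05.

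The Bonferroni step depends on a significance criterion, and this sentence is the only candidate for one. The article also presents itself, in the Introduction, as a basis for standardisation and replication by other institutions, so the sentence may be copied. What is at stake is the prespecified type I error rate: a reader of the results should be able to check a claim of significance against a rule fixed beforehand, and the published rule does not allow that as it stands.

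**Working it through.** This is mainly a check of wording, with one short calculation to size the literal reading.

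**Inputs**

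| Input | Value | Source |
|---|---|---|
| Cut-off | 0.05 | Section 2.10 |
| Direction | p greater than the cut-off | Section 2.10 |
| Label | statistical power | Section 2.10 |
| Use of the criterion | selects variables for the Bonferroni step | Section 2.10 |
| Group sizes | 15 and 15 | Section 2.9.6 |

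**Step 1. Read the sentence as a statement about power.** Power above 0.05 is not a usable target. Any two-sided test at the 0.05 level already exceeds it for every non-zero effect, so on this reading the sentence constrains nothing. It would also leave the Bonferroni step without a criterion.

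**Step 2. Read it as the significance criterion.** Under a true null hypothesis, p from a valid continuous test is uniform on (0, 1). Hence

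- conventional rule: P(p < 0.05 | null) = 0.05;
- rule as written: P(p > 0.05 | null) = 1 − 0.05 = 0.95.

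The ratio is 0.95 / 0.05 = 19.

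**Step 3. Check by simulation.** In 100,000 simulated two-sample t-tests with 15 per group and no true difference, p < 0.05 occurred in a fraction 0.04866 and p > 0.05 in 0.95134. Both agree with step 2. The t-test stands in for the mixed ANOVA. The argument from uniformity does not depend on which valid test is used.

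**Step 4. Look for a correction elsewhere.** Section 2.9.6 gives the group sizes and the software but no significance level. The figure 0.05 appears nowhere else in the article. The intended rule can be guessed from convention but not recovered from the text.

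The article gives no type I error figure of its own to reproduce. The result is that neither reading of the sentence yields a workable criterion.

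**The case against.** The strongest reply is that this is a language slip with an obvious meaning. The Bonferroni step is meant to find which assessments differ, so significance is evidently used in its ordinary sense. The methods and software are conventional. The article has other slips of the same kind: the Abstract transposes the abbreviation for Parkinson's disease, and the Introduction and Discussion misspell the one for interval training. The same sentence also promises effect sizes, so the threshold is not the only evidence that will be reported.

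Most of this stands, and it limits the point in two ways.

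- A reader might infer that the trial would declare null results positive. The documents do not support that. The sentence never says that results above 0.05 are significant. The 95% figure describes a literal reading, not the expected conduct of the analysis.
- A reader might also infer from the misuse of the word power that the trial has no planned power or too little of it. This sentence cannot carry that inference. The inputs to the sample size calculation may be in a full protocol or analysis plan that is not shown, and a condensed article may leave them there.

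The reply does not remove the error. This is text that is stated wrongly, not detail left to another document. A probable intention is also not a recorded rule: even if 0.05 is taken as the intended level, the sidedness remains unstated.

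**Conclusion.** Wrong as written. Section 2.10 mislabels the significance level as power and reverses the inequality. It is the only inferential threshold in the article, and the Bonferroni step relies on such a threshold.

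Read literally as that criterion, it would be met by 95% of true-null tests instead of 5%. This figure assumes a valid test with a uniform null distribution of p, and it applies to each test separately. The likely practical effect is smaller: readers will assume p < 0.05, and the prespecified rule stays uncertain in sidedness and formally incorrect in print. That the error exists is certain. That the sentence was meant as p < 0.05 is a reasonable inference, which the sponsor should confirm.

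**What to change.** In Section 2.10, replace the part of the sentence that sets the threshold with:

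> Tests are two-sided with a significance level of alpha = 0.05; a difference is declared statistically significant when p < 0.05.

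The sponsor should confirm both the level and the sidedness. The word power should be removed from this sentence. The commitment to show effect sizes can stay as it is.

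The cost is one sentence. It changes neither the sample size nor the choice of model or data collection. It should be made before the results are analysed, so that the rule is on record beforehand.
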